### Provisions for post-trial care {30}

After completing the EMDR intervention, the therapist evaluates the effects of treatment with the participant, his/her parents and the responsible practitioner. The therapist also consults the multidisciplinary staff to jointly decide if further treatment is indicated, and if so further treatment will be offered.

### Outcomes {12}

Table 1 presents an overview of assessment instruments used for each measurement time. Details of instruments are described below.

**Table 1. Tab1:**
[figure not shown]
Assessment instruments

#### Primary outcome measures

##### **Depressive****symptoms**

The Dutch version [37] of the Children’s Depression Inventory-2 (CDI-2, Child and Parent Version) [38] will be used to assess affective, behavioural and cognitive aspects of depressive symptoms in the past 2 weeks. The CDI-2 includes 28 items dealing with sadness, self-blame, loss of appetite, insomnia, interpersonal relationships and school adjustment. The adolescent is asked to choose one of three sentences that best fits her/his feelings, thoughts and behaviours (e.g. “I am sad all the time”) in the past 2 weeks. These items are scored on a 3-point Likert scale (0–2, total range 0–56). The CDI-2 has good internal consistency and convergent validity [39]. For the Dutch version, internal consistency, test–retest reliability and convergent and divergent validity are high. For the parent version, internal consistency was high and convergent and divergent validity were moderate [37].

##### Structured interview for depression and comorbid disorders

The Schedule for Affective Disorders and Schizophrenia for School Age Children Present and Lifetime Version (K-SADS-PL-5) is a semi-structured diagnostic interview designed to assess current and lifetime diagnoses for affective, psychotic, anxiety, behavioural, substance abuse and eating disorders [40]. The clinician-based computer version of the K-SADS-PL-5 is used. For the purpose of the current study, questions about traumatic interpersonal experiences that have been identified as being connected to the onset of depressive episodes [25] (i.e. loss, separation and humiliation (being bullied/isolated/ignored), will be added to the K-SADS-PL-5 PTSD section.

The complete Youth Version is administered during pre-intervention assessment; at post-intervention and follow-up assessments, only the Depressive Disorders section, and the supplements for Suicidality and Sleep problems are administered.

All assessors are trained according to a programme consisting of observing live K-SADS COMP interviews and several supervised interviews. Each K-SADS COMP report will be reviewed and discussed by a supervisor. Moreover, all assessors attend 6-weekly intervision meetings.

#### Secondary outcome measures

##### Anxiety symptoms

The Dutch version of the revised Screen for Child Anxiety Related Emotional Disorders (SCARED-NL, Child and Parent Version) is used to assess signs of anxiety disorders in the past 3 months [41, 42]. The SCARED-NL is a 69-item inventory rated on a 3-point Likert-type scale (0 = ‘not true’ or ‘hardly ever true’; 1 = ‘somewhat true’ or ‘sometimes true’; 2 = ‘very true’ or ‘often true’; total range 0–82). Good psychometric properties (excellent internal consistency, large test–retest reliability and moderate to large parent–child agreement rates) of different versions of the SCARED were demonstrated in a large meta-analysis [43] and specifically for the Dutch version used in this study [42]. A 5-factor structure (panic/somatic, generalized anxiety, separation anxiety, social phobia, and school phobia) has been found repeatedly and has also been confirmed for the Dutch version. Since the reduced 5-item version of the SCARED has similar psychometrics to the full SCARED [44], the 5-item version will be used in this study.

##### Post-traumatic stress symptoms

The Dutch version of the Child and Adolescent Trauma Screen (CATS; Child and Parent Version) [45] explores individual trauma history using a checklist of 15 potentially traumatic events and frequency of each of 20 post traumatic stress symptoms, using a 4-point response scale ranging from 0 = never to 3 = almost always. The CATS has good to excellent reliability and sufficient convergent-discriminant validity for both self- and parent-report [45]. The psychometric qualities of the Dutch version are currently studied.

##### Global assessment of psychological problems

The Dutch adolescent version [46] of the Strengths and Difficulties Questionnaire (SDQ, Child and Parent Version) [47] is used as a global assessment of psychological problems. The SDQ consists of 25 items which are scored on a 3-point Likert scale ranging from ‘not true’, ‘somewhat true’ or ‘certainly true’ (total range 20–80). In this study’s analyses, the ‘total difficulties scale’ is used. The parent and self-report versions have an internal consistency that is generally acceptable in Dutch samples [46].

#### Predictors

##### Experiences of emotional neglect and emotional abuse

The Dutch version [48] of the Childhood Trauma Questionnaire (CTQ) [49] was adapted for adolescents and used to assess experiences of childhood maltreatment. The CTQ is a self-report list consisting of 28 items which are scored on a 5-point Likert scale. The CTQ has a good criterion validity in both a clinical and a healthy sample [50]. In the analyses, the subscales ‘Emotional neglect’ (range 5–25) and ‘Emotional abuse’ (range 5–25) are used. Internal consistency of these subscales were high in a Dutch sample [51].

##### Family functioning

The Dutch version [52] of the Family Assessment Device (FAD; Child and Parent Version) [53] is used to assess structural, organizational and transactional characteristics of families. The questionnaire covers 6 dimensions: affective involvement, affective responsiveness, behavioural control, communication, problem solving and roles. In addition, there is a 7th scale measuring general family functioning. Both dimension scores and the general functioning scale are used in the analyses. The FAD comprises 60 items rated on a 4-point scale. Scale scores are computed by adding the responses and dividing by the number of items in the scale with higher scores indicating worse levels of family functioning. The psychometric qualities of the English version have been studied extensively and were satisfactory to good [53, 54]. Results from studies on the Dutch version [55] were comparable.

### Participant timeline {13}

Figure 1 shows the participant timeline.

### Sample size {14}

A power analysis is calculated with G-Power. With the following assumptions: ANOVA with 2 groups and (EMDR and waiting list), 2 points of measurement (baseline and after treatment), the CDI-2 total score as outcome measure, effect size of F = 0.40, a power of 0.095 with *α* = 0.05, a total of 48 participants (24 participants per group) will be needed. In line with the drop-out rate (21.6%) we had in our first clinical study [35] and by those reported in previous intervention studies using EMDR with MDD patients (23% [26], 30% [29], 15% [30]), a maximum of 30% drop-out during treatment and follow-up trajectory is expected. Consequently, 64 adolescents will be included in the study, equally divided between EMDR and waiting list condition.

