## Assignment of interventions: allocation

### Sequence generation {16a}

Randomization will be performed as block randomization with a 1:1 allocation stratified per treatment location. An independent researcher will conduct randomized allocation by using the SPSS function to produce random numbers. To reduce predictability of a random sequence, details of any planned restriction (e.g. blocking) will be provided in a separate document that is only available to those who enrol participants and assign interventions. Hence, the researchers conducting the assessments will be blind to the randomization process. Randomization will take place in blocks of 10 participants.

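### Sample size: the printed power of 0.095 cannot go with 48 participants, 64 covers 25% drop-out and not the stated 30%, and 48 cannot be reproduced from the inputs given

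*Protocol article*

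**What the plan says.** The Sample size section (item 14) of the protocol article gives the only justification for the trial's size. It describes a G-Power calculation for an "ANOVA with 2 groups and (EMDR and waiting list), 2 points of measurement (baseline and after treatment"), with the CDI-2 total score as outcome. The remaining inputs are "effect size of F = 0.40, a power of 0.095 with" a significance level of 0.05, and the result is that "a total of 48 participants (24 participants per group) will be needed".

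The section then cites drop-out of 21.6% in the group's own earlier study and of 23%, 30% and 15% in other EMDR studies, and concludes: "a maximum of 30% drop-out during treatment and follow-up trajectory is expected. Consequently, 64 adolescents will be included in the study", split equally between the arms. The target of 64 is repeated in the Abstract and in the registry entry under Administrative information.

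The section names neither the G-Power ANOVA option nor the correlation assumed between the two measurements. No other section corrects the power or the drop-out step.

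**The concern.** Three numbers carry the justification: the power, the evaluable number and the drop-out allowance. They do not fit together. The power is below any level a trial would plan for. The step from 48 to 64 is presented as following from 30% drop-out, but it does not. And a reader who guesses that 0.95 was meant and tries to recover 48 does not arrive there at the usual settings.

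What is at stake is how the result will be read. A null finding is judged against the planned power, and here that power is misprinted and cannot be reconstructed. If the stated maximum loss occurs, the trial also ends below the number its own calculation calls necessary.

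**Working it through.** **Inputs from the protocol.** f = 0.40 (printed as F), alpha = 0.05, two groups, two measurements (m = 2), 1:1 allocation (Sequence generation, item 16a), 48 evaluable, 30% maximum drop-out, 64 randomised.

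**Assumed, because not stated.** The ANOVA option, and the T0–T1 correlation ρ (0.5 below unless varied). Reading 0.095 as 0.95 is also an assumption.

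**Step 1: the drop-out allowance (no statistical assumption).** The number to randomise is n/(1 − loss).

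- 48/(1 − 0.30) = 68.6, so 69, or 70 for equal arms.
- 64 × 0.70 = 44.8. Per arm, 32 × 0.70 = 22.4, so about 22 against the 24 required, or 44 in total.
- 64 × 0.75 = 48 exactly, so 64 is the number for 25% loss.
- 48 × 1.30 = 62.4, which becomes 64 when rounded up to equal arms. Multiplying by 1.3 instead of dividing by 0.7 would explain the figure, but that is a guess.

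**Step 2: the printed power.** The power of the F test comes from the noncentral F distribution with 1 and N − 2 degrees of freedom and noncentrality λ:

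- one-way ANOVA: λ = f²N
- repeated measures, between factors: λ = f²N·2/(1 + ρ)
- repeated measures, group × time interaction: λ = f²N·2/(1 − ρ)

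A power of 0.095 is reached at N = 6 for the first two and N = 4 for the third (ρ = 0.5). It cannot be the target behind 48.

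**Step 3: trying to reproduce 48.** With N = 48, f² = 0.16 and ρ = 0.5, λ is 0.16 × 48 = 7.68 (one-way), 7.68 × 2/1.5 = 10.24 (between factors) and 7.68 × 2/0.5 = 30.72 (interaction).

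| Option (f = 0.40, alpha 0.05) | Total N for power 0.95 | Power at 48 | Power at 44 |
|---|---|---|---|
| One-way ANOVA | 84 | 0.774 | 0.736 |
| Between factors, ρ = 0.5 | 64 | 0.880 | 0.849 |
| Group × time interaction, ρ = 0.5 | 24 | 0.9997 | 0.999 |

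None of these gives 48. For the between-factors test at ρ = 0.5, lower targets of 0.80, 0.85 and 0.90 give 40, 46 and 52, so they do not give 48 either.

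**Step 4: settings that do give 48.** For the between-factors test the smallest even total is 48 at each of these pairs:

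| Target power | ρ |
|---|---|
| 0.95 | about 0.1 (0.09 to 0.13) |
| 0.90 | 0.4 |
| 0.85 | 0.6 |
| 0.80 | 0.8 |

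The interaction test gives 48 at 0.95 only with a slightly negative ρ (about −0.1). So 48 is attainable, but each route needs a correlation, and in most cases a power, that the section does not state.

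**The case against.** The strongest reply is that little of this is demonstrated error. The power is an obvious misprint. The ANOVA option and correlation are details that an article may leave to the full protocol, and 48 lies inside the range that plausible settings produce. That is right as far as it goes: 48 is not shown to be wrong, and the missing settings would not make a point by themselves. They matter here because the printed power is unusable, so without them the intended target cannot be recovered.

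On drop-out, the 30% is an upper limit over treatment and follow-up together, whereas the power calculation uses only baseline and post-treatment. At the other cited rates 64 is enough: 64 × 0.784 = 50.2, 64 × 0.77 = 49.3 and 64 × 0.85 = 54.4. Participants who stop treatment are asked to continue measurements, and data up to withdrawal are used. All this limits the practical consequence. It does not repair the text, which derives 64 from the 30% and gives no separate figure for loss by T1.

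A reader might go further and infer that the trial is underpowered, for instance by translating f = 0.40 into a standardised T1 difference of 0.80 and computing power for that. The documents do not support this. They state no such difference and specify no baseline-adjusted test; the protocol names a linear mixed model and says no covariates will be used to adjust for confounding. At the stated f, 48 is more than enough for the interaction test at ρ = 0.5. Such figures could serve at most as a labelled sensitivity range.

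**Conclusion.** Two errors stand on the text alone. The printed power of 0.095 is incompatible with 48 participants. The 64 does not follow from 48 and 30% drop-out: it is 6 short of the 70 that equal arms would need, and at 30% loss it leaves 3 to 4 fewer than the 48 required, about 7%.

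A third point stands in weaker form: 48 is not reproducible from the stated inputs. This rests on reading 0.095 as 0.95 and, for two of the three options, on an assumed correlation of 0.5.

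The effect on power of falling from 48 to 44 is small at the stated effect size: 0.88 to 0.85 for the between-factors test at ρ = 0.5, and above 0.99 at both sizes for the interaction. The defect is in the stated justification. It is not evidence that 64 is too few.

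**What to change.** Keep 64 and rewrite the section:

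- State that 64 are randomised, giving 48 analysable if drop-out is at most 25% and about 44 at 30%.
- Replace 0.095 with the power actually targeted.
- Name the G-Power ANOVA option and the T0–T1 correlation used, and write the effect size as f.
- Give the power those inputs yield at 48 and at 44. If they were the between-factors test with a correlation of 0.5, the values would be 0.88 and 0.85. The authors must supply their own settings.
- State the loss assumed by T1, which bears on the calculation as described, separately from the loss over the whole follow-up.

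The cost is wording only. No extra participants are needed, which matters because inclusion was expected to finish in April 2023 (Trial status). The stated power may come out lower than 0.95, if that was the intended figure.

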### Recruitment {15}

Adolescents will be referred by their general practitioner and receive a regular intake appointment. After this intake, a preliminary diagnosis is formulated and discussed in a multidisciplinary team. Further assessment (either psychological, psychiatric, family assessment or observational assessment at home or at school) is initiated on indication. At least, a clinician-based K-SADS-PL-5 interview will be conducted. In case both a major depressive disorder and memories of at least one distressing or traumatic event related to the depressive symptomatology are identified, the adolescents and their parents will be approached by the researcher or research assistant. They will explain the purpose of this study. If the adolescent (age 12–16 parents also need to sign) and the parents decide to participate, they will both sign the informed consent.

Expected recruitment will be 1–3 patients per month and expected duration of inclusion is 30 months.

## Assignment of interventions: allocation

### Sequence generation {16a}

Randomization will be performed as block randomization with a 1:1 allocation stratified per treatment location. An independent researcher will conduct randomized allocation by using the SPSS function to produce random numbers. To reduce predictability of a random sequence, details of any planned restriction (e.g. blocking) will be provided in a separate document that is only available to those who enrol participants and assign interventions. Hence, the researchers conducting the assessments will be blind to the randomization process. Randomization will take place in blocks of 10 participants.

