### Who will take informed consent? {26a}

Prior to the study, potential participants and their parents will be approached by the researcher or the research assistant and receive oral and written information about the content, purpose and research design. If all parties agree, informed consent will be signed by both participants and their parents.

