### Concealment mechanism {16b}

Due to the nature of the trial, participants and therapists in the study cannot be blinded for condition. Assessors and therapists will emphasize the importance of blinding to the participants and remind them not to reveal the randomized treatment condition to the assessors. Therapists are supported by the principal investigator, who is not involved in the execution of the assessments. Assessors will be asked to report any case of unblinding, in which case, another assessor will repeat the entire measurement. The use of a validated password file which is not accessible for those involved in the assessment will ensure concealment until the randomization result is revealed.

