## Oversight and monitoring

### Composition of the coordinating centre and trial steering committee {5d}

The research teams consist of the principal investigator (CP), a clinical psychologist in training (MK), two senior researchers (CdR, AD), a professor of an affiliated university (BE) and a research assistant (MV). The principal investigator is responsible for daily monitoring, for contact with the independent researcher performing the randomization, and for all contacts with participating practitioners. Assessments will be coordinated by the second investigator (MK) and the research assistant to guarantee blindness to treatment condition. The research team bimonthly evaluates the progress of the study. The local principal investigator of participating institution GGZ Delfland (MB) was involved in the design of the study and will be involved in the practical implementation of the study and in the reporting of the results.

For participants, an independent expert is available for questions about the trial.

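### The access rule for blocking details is stated the wrong way round: it gives them to the staff who enrol and assign, in an open-label trial with a published fixed block of 10

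*Protocol article*

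**What the plan says.** All references are to the protocol article.

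- **Sequence generation {16a}.** The method is "block randomization with a 1:1 allocation stratified per treatment location". The access sentence begins "To reduce predictability of a random sequence, details of any planned restriction (e.g. blocking" and continues that these details will be "provided in a separate document that is only available to those who enrol participants and assign interventions". It is followed by "Hence, the researchers conducting the assessments will be blind to the randomization process" and by "Randomization will take place in blocks of 10 participants".
- **Trial design {8}.** This section repeats the block size of 10 but draws a different conclusion: the main researcher is the one kept blind to how randomization is done. Participants learn their group after the baseline assessment (T0), which follows consent.
- **Concealment mechanism {16b}.** Concealment rests on a "validated password file which is not accessible for those involved in the assessment". Participants and therapists know the arm.
- **Implementation {16c}.** An independent researcher randomizes and notifies only the trial coordinator, who tells the therapist and the participant.
- **Who will take informed consent? {26a}.** It states that "potential participants and their parents will be approached by the researcher or the research assistant". Recruitment {15} says the same.
- **Composition of the coordinating centre and trial steering committee {5d}.** Assessments are coordinated by the second investigator "and the research assistant to guarantee blindness to treatment condition".
- **Procedure for unblinding {17b}.** The design is open label, with only assessors and analysts blinded.

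**The concern.** Concealing allocation before enrolment and blinding assessors after it are separate safeguards. The access sentence in {16a} announces the first, but its conclusion speaks only to the second. Taken literally, it gives the restriction details to the people who decide whom to approach and when. Anyone following it would set the file permissions the wrong way.

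An enroller who can anticipate the next arm can, even without meaning to, bring forward, delay or pass over a candidate. Two features make this more than a formality. The comparator is a waiting list, so staff may have a preference for a particular patient. Entry also depends partly on judging whether a distressing memory is connected to the depression. The section on missing data {20c} relies on randomization to justify analysis without covariate adjustment, so the comparison depends on allocation being intact.

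**Working it through.** The documents give no predictability figure to reproduce. The check has two parts.

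**1. Does any other section repair the rule?**

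- {16b} closes the password file to assessment staff. Enrolling staff are not excluded.
- {8} says the main researcher is blind to the process. This conflicts with an access rule that opens the restriction details to those who enrol and assign, and it neither withdraws nor limits that rule.
- {16c} keeps randomization with an independent researcher and narrows who is told each result. It does not say who may see the restriction details.

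No section reverses the sentence.

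**2. How predictable is the sequence to someone who knows the block size and the earlier allocations in the stratum?**

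Inputs: block of 10, 1:1, so 5 per arm ({16a}); total 64 (Sample size {14}). The stratum is the treatment location. That could mean the two institutions or the 4 + 5 = 9 locations listed under Study setting {9}. The text does not settle it, so both are shown. An even spread over strata is an assumption.

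After k allocations in a block, the number a already in one arm has probability C(5,a)·C(5,k−a)/C(10,k). The next allocation is certain when one arm has used all 5 places. The best guess is the arm with more places left, and it is right with probability max(5−a, 5−k+a)/(10−k), averaged over a.

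For example, the 8th allocation (k = 7) is certain with probability 2·C(5,2)/C(10,7) = 20/120 = 0.1667, and the 9th (k = 8) with probability 2·C(5,3)/C(10,8) = 20/45 = 0.4444.

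| Position in block | P(certain) | P(best guess right) |
|---|---|---|
| 1 | 0 | 0.5000 |
| 2 | 0 | 0.5556 |
| 3 | 0 | 0.5556 |
| 4 | 0 | 0.5952 |
| 5 | 0 | 0.5952 |
| 6 | 0.0079 | 0.6429 |
| 7 | 0.0476 | 0.6429 |
| 8 | 0.1667 | 0.7222 |
| 9 | 0.4444 | 0.7222 |
| 10 | 1.0000 | 1.0000 |
| Sum, full block | 1.67 | 6.53 |

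The first sum agrees with the closed form 2m/(m+1) = 10/6 = 1.67 for m = 5.

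*Two strata of 32* (each 3 full blocks plus 2 allocations):
- Certain: 2 × 3 × 1.67 = 10.0 of 64, or 15.6%.
- Right guesses: 2 × (3 × 6.532 + 0.500 + 0.556) = 41.3 of 64, or 64.5%.

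*Nine strata* (eight of 7 and one of 8, so 8 × 7 + 8 = 64; no block fills):
- Certain: 8 × (0.0079 + 0.0476) + (0.0079 + 0.0476 + 0.1667) = 0.444 + 0.222 = 0.67 of 64, or 1.0%.
- Right guesses: positions 1 to 7 sum to 4.087, so 8 × 4.087 + (4.087 + 0.722) = 37.5 of 64, or 58.6%.

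Unrestricted 1:1 randomization would give no certain allocations and 50% right guesses.

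**The case against.** The strongest reply is that this is a slip of wording. The sentence opens with the right aim, an independent researcher generates and performs the randomization, {8} says the main researcher is blind, and the arm is revealed only after consent and T0. That may well be so. But the sentence as published is the rule, and nothing else in the text puts it right.

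The second reply is that the counting mechanism is not shown for the named enrollers, and this stands. Prediction needs the earlier allocations in the stratum as well as the block size. The text documents that knowledge for the trial coordinator across the trial, and for therapists and participants in their own cases. The research assistant is not in the notification chain in {16c}, and the text does not say whether the researcher who approaches families is also the coordinator. The figures above are therefore conditional.

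A reader might go further and infer three things that the documents do not support:

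- *That enrolling staff hold the list.* The rule covers details of the restriction, not the sequence.
- *That the assessors' blind is broken because the research assistant both approaches families and helps coordinate assessments.* Knowing a block size does not reveal a participant's arm.
- *That selection bias occurred.* Candidates reach the researcher only after intake, team discussion and a diagnostic interview, and late disclosure limits manipulation after consent. What remains possible is influence on who is approached and when.

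**Conclusion.** The point holds. The access rule in {16a} contradicts the aim given in its own sentence, is not corrected elsewhere, and would weaken allocation concealment if followed. It must be reconciled with {8} and {16b}.

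For a person who enrols, knows the block size and knows earlier allocations in the stratum, about 1% to 16% of the 64 allocations would be certain and about 59% to 65% of best guesses would be right. The lower end takes the nine locations as strata and the upper end the two institutions, each with an even spread of participants. It would be wrong to present the full-block result, about one allocation in six, as the trial's figure without these conditions. Independent randomization and late disclosure lower the risk. They do not prevent anticipation before a family is approached.

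**What to change.** 1. In {16a}, reverse the sentence: the restriction details and the sequence are held only by the independent researcher and are unavailable to anyone who approaches, consents or enrols participants, or who coordinates or performs assessments.
2. In {16b}, extend the password-file restriction to enrolling staff, and bring the statement in {8} about who is blind into line.
3. In the trial report, state who had access to the restriction details and to earlier allocations. If the published sentence is a slip and access was in fact withheld, say so.
4. If allocations remain, the independent researcher can use varying, undisclosed block sizes, since the size of 10 is now public.

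Items 1 to 3 cost a few sentences and a change of file permissions, with no extra patients. Item 4 is a refinement with limited reach: inclusion began in November 2020 and was due to end in April 2023 (Trial status), and protocol version 2 is dated October 2022, about 23 of 30 months in. If it counts as a substantial modification, {25} requires ethics committee approval first.
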